#### Adaptation of the PA4E1 program school practices and implementation support intervention for implementation at scale

For this study, minor adaptations were made to the school physical activity promoting practices to address barriers raised regarding their implementation identified in the original trial. The multi-component implementation support strategies were similarly adapted to address barriers to their delivery and utility in the original trial, and to aid their implementation at-scale. The adaptations were made based on a review of existing models and factors for scaling up public health interventions [43] and a scoping review of frameworks for adapting public health interventions [44].

The key steps for adapting the implementation support strategies were undertaken iteratively, and involved: i) identifying barriers and enablers to change based on a review of the literature, focus groups with PE teachers and students, key informant interviews with school executives participating in the initial trial and Aboriginal stakeholder meetings and; ii) using the Theoretical Domains Framework (TDF) [40] and Behaviour Change Wheel (BCW) [39] to map the identified barriers to school implementation of PA practices and to evidence based implementation support strategies (behaviour change techniques); iii) revising the PA practices and implementation support strategies and delivery modes based on scalability (using the APPEASE criteria [45]) and iv review of the resulting adaptations by expert researchers and practitioners.

The main adaptations to the school physical activity promotion practices were: a broader focus on quality PE [41] rather than solely on ‘active PE’; and the use of a modified enhanced school sport program developed in partnership with the NSW Department of Education, designed to meet the needs of schools and supported by the Education system known as ‘Resistance Training for Teens’ [46] (rather than Program X [16]). These adaptations were made to support delivery at scale and synchronise with existing systems.

Adaptations to the multi-component implementation support intervention strategies were: 1) embedding school staff by appointing and funding an in-School Champion along with access to a local health promotion Support Officer to replace the external change agent model used in the original trial; 2) a change in the modality of teacher professional learning from face-to-face training to online where possible, and use of accredited education sector courses where possible rather than project specific learning programs, to allow teachers to include attendance at these courses within their professional accreditation [38]; 3) the provision of tools (such as PE observation forms) and resources via a program website rather than paper-based; 4) prompts and reminders and performance monitoring and feedback automated to each school (via completion of termly progress surveys) to occur via the program website rather than verbal/email prompts and manually generated feedback reports.

Additional file 1: Table S1 presents an overview of the identified barriers to school implementation and scale-up, the mapping of these barriers to the TDF [40] and BCW [39], the behaviour change techniques selected to address the barriers, and a further description of how these have been incorporated into the multi-component implementation support intervention used in the current trial.

### Control group

Control schools will participate in study measures and continue delivering usual PE lessons, school sport and other PA programs and practices. PA4E1 program materials, inclusive of access to the program website will be available to these schools on study completion.

### Data collection procedures and measures

An overview of data collection is shown in Table 3. The primary outcome will be the proportion of schools in each group implementing any four of the seven PA practices (the prior trial showed a significant effect on student MVPA at 12 month mid-point [47], by which time schools had implemented 4 of the 7 practices). Secondary outcomes will be the mean number of PA practices achieved, whether or not schools implement each of the seven PA practices (to determine compliance with each practice), as well as student level outcomes (objectively measured PA and adiposity indicators). Economic outcomes will include: 1) the direct cost of the multi-component implementation support intervention from multiple stakeholder perspectives; 2) average and incremental cost-effectiveness ratios, subject to assessment of effectiveness, and 3) budget impact calculated from a public finance perspective.

**Table 3 Tab3:**
[figure not shown]
Schedule of study data collection and measures

^a^Data collection planned but dependant on additional funding

A separate process evaluation protocol will be developed and published elsewhere.

#### School characteristics/ Head PE teacher characteristics

Publicly available data [37] will provide information on school sector, postcode, size (total enrolments), Indigenous enrolments, and students who speak a LOTE at home enrolment for all schools approached for consent. For schools participating in the project the following characteristics will be obtained through a Head PE teacher computer assisted telephone interview: number of PE teachers and full time equivalent PE positions; language groups most commonly represented when the school has more than 10% of LOTE students.

Computer assisted telephone interviews with Head PE teachers and online surveys with all PE teachers conducted at baseline, 12 and 24 months, will ask for background information including sex, PE training, years of teaching experience, how long they’ve taught PE at their current school, and grades they teach in the current year.

#### School practices

Measures of the seven PA practices shown in Table 1 will be undertaken via the computer assisted telephone interviews with Head PE teachers, administered by trained interviewers. The items will be adapted from those used to collect process data in the previous PA4E1 trial [15, 25, 47] and will be forwarded by email to participants prior to the interview.

#### Student level variables (nested sub study)

*Physical activity:* Whole-day objective PA measurement will be undertaken using wrist worn Actigraph GT9X-BT or GT3X+ accelerometers [48], distributed to students at school within class, at the same time as students’ complete anthropometric measures and surveys. Accelerometers have displayed acceptable intra- and inter-instrumental reliability and provide a valid and reliable estimate of PA in young people [48, 49]. Students will be asked by trained research assistants to wear the accelerometers on their non-dominant wrist during waking hours for seven consecutive days. To improve compliance, student and/ or parent mobile phone numbers will be requested via the consent form, and a text message sent by the researchers each morning reminding students to wear the accelerometer [15]. School start and finish times that apply during the assessment period will be requested from schools.

#### Anthropometric data

Research assistants will be trained in measuring height and weight (used to calculate body mass index; BMI) using the International Society for the Advancement of Kinanthropometry (ISAK) procedures [50]. Where possible, all measurements will be taken in the morning [51]. Weight will be measured in light clothing without shoes using a portable digital scale (Model no. UC-321PC, A&D Company Ltd., Tokyo Japan) to the nearest 0.1 kg. Height will be recorded to the nearest 0.1 cm using a portable stadiometer (Model no. PE087, Mentone Educational Centre, Australia). The physical assessments will be conducted in a sensitive manner, with student measurements taken behind a privacy screen. Body mass index (BMI) will be calculated as weight/height squared (kg/m^2^). Weight status will be determined using International Obesity Taskforce definitions [52].

#### Survey

The student survey, which will take approximately 20 min, will be undertaken to assess: student socio-demographic characteristics (age, sex, Aboriginal or Torres Strait Islander status, languages spoken at home, postcode of residence); which years they have attended the school; self-reported PA [53]; school PA behaviour (items from Questionnaire Assessing School Physical Activity Environment Q-SPACE [54]); autonomous motivation for PA (intrinsic motivation and identified regulation subscales of the Behavioural Regulation in Exercise Questionnaire 2 (BREQ-2) [55]), social support for PA [56]; perceptions of school PA environment (items from or adapted from scales including Q- SPACE [54], Student Engagement in School Questionnaire [57], Teacher as Social Context questionnaire [58] controlling teacher scale [59]; and general health and well-being (KIDSCREEN 10 [60]). The survey will be completed by students at 12 and 24-months via a tablet provided by the research team.

#### Cost data

Cost data pertaining to the development and implementation of the intervention will be collected prospectively using a resource use capture tool. The tool, developed in MS Excel (2013), allows the input of resource use data from each of the stakeholders involved in implementing the intervention for the following cost categories: labour (health service), labour (non-health service), materials, joint costs and miscellaneous costs. Management logs routinely used by the Support Officers will inform the identification and measurement of resource use associated with the intervention. Interviews and surveys with teachers will also inform the identification and measurement of resource use from the perspective of the schools.

#### Implementation process outcomes

A full process evaluation protocol, with detailed aims, will be published separately. Briefly, the evaluation of implementation outcomes for the trial will be aligned to the assessment of domains recommended by Proctor et al. 2011 [61] including appropriateness, acceptability, adoption, feasibility, fidelity, penetration (reach) and sustainability. In addition, usability and engagement with the program website will be investigated [62]. A mixed-methods assessment will use data obtained from a variety of sources including PE Teacher and in-School Champion termly implementation surveys from program schools (Table 3). Appropriateness, acceptability and feasibility will be assessed using validated survey items developed by Wiener et al. [63]. Adoption (primary trial outcome) will be assessed via computer assisted telephone interviews with Head PE teachers. Fidelity and dosage (and context) will be assessed via a fidelity monitoring log [64] and a project specific fidelity checklist. Reach and sustainability will be assessed using items developed by the project team, specific to the program. Qualitative data sources will include in-School Champion focus groups and semi-structured interviews with PE teachers, as well as talk-aloud surveys relating to the engagement, usability and user experience with the program website.

The online surveys of PE teachers in program and control schools will provide data on practice barriers (Table 3).

#### Supporting schools with data collection

All schools will be offered half a day of teacher relief ($175AUD) at each practice data collection point (baseline, mid-point and follow-up) to reimburse the school for their time in assisting with data collection. In addition, schools participating in student data collection (nested sub study) will be offered 1.5 days teacher relief ($525AUD) at each of the 12 and 24 month collections, plus additional funding if school staff are involved in parent consent gaining calls. This will allow a school staff member to be present during the student data collection sessions. Prior to data collection days, a list of students with parental consent will be provided to the school so schools can consider whether additional research staff may be required to assist students with limited literacy.

### Statistical analyses

School characteristics will be summarised separately for schools participating in the trial and those refusing participation, and for program and control schools. Student characteristics (nested sample) will also be summarised for each group for the 12 month (Grade 8) and 24 month (Grade 9) samples.

#### Primary outcomes

The primary outcome is the proportion of schools implementing at least four of the seven PA practices [47] based on the Head PE teacher computer assisted telephone interview data. The analysis will follow intention-to-treat principles, with multiple imputation the primary method of dealing with missing data. Per protocol analyses will also be performed, based on those schools receiving the full implementation support intervention.

Differences between treatment groups in the primary outcome at 12 and 24-months will be assessed using generalised linear regression models (a separate analysis conducted for each time point). A log link and binomial distribution function will be used (a logistic link will be utilised if the analysis model fails convergence). The stratification variables will be included in the models as covariates.

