### Randomisation

Consenting schools will be randomised to either program or control condition using a random number function in Microsoft Excel. Block randomisation (1:1) will be undertaken within the strata (four local health districts and two school sectors). Principals will be notified of their school allocation following baseline collection of school practice measures. Schools consenting to student level data (nested study) will be randomly selected within strata using a random number generator in Excel, and at stratum sizes proportional to that observed in the main study. Schools will be notified of student level measurement involvement when notified of group allocation.

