#### Cost effectiveness analysis

Subject to assessment of effectiveness, the trial-based evaluation will include assessment of cost-effectiveness. It has been suggested that one of the ways to improve efficiency in conducting economic evaluations of implementation interventions, is to confine the study to measures of the care process or intermediate outcomes [70]. This is the approach adopted in this study, where the cost-effectiveness outcomes, the incremental cost effectiveness ratios (ICER) will be: (i) incremental cost per percent change in the proportion of schools implementing at least four of the seven PA practices, reflective of the primary trial outcome and (ii) incremental cost per unit changes in student-level outcomes (minutes of MVPA per day, % reduction in BMI and metabolic equivalent (MET) hours gained). The ICERs will be calculated as the arithmetic mean difference in cost between the intervention and usual practice arms divided by the arithmetic mean difference in effect [68, 71].

Uncertainty analysis will be conducted using parametric and non-parametric bootstrapping techniques and sensitivity analyses will be conducted to explore the robustness of the economic outcomes to any uncertainty associated with key parameters.

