### Sample size

Based on publicly available data there are approximately 120 potentially eligible schools. Based on school consent rates in previous trials conducted by the researchers of around 65–70% [15], a sample of 76 schools (38 per arm) will provide 80% power to detect an absolute increase of ~ 35% between groups in the proportion of schools implementing at least 4 of the 7 items at 12 and 24-months (alpha 0.025 to allow for program effect at 12 or 24 months). Without prior data on baseline levels of school practices, this calculation makes the conservative assumption that 40% of schools in the usual care arm achieve this target at follow-up.

For student level variables it is estimated that a nested sample of 30 schools and a student consent rate of 65% will yield about 1200 students (600 per group) with valid accelerometer data. Using an ICC of 0.03 [15] and a standard deviation of 23 min of MVPA, will allow a 6.2 min [47] difference in the mean difference between groups at each separate follow-up to be detected with 80% power and a 2.5% type 1 error rate.

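### The primary model's link-switching rule lets convergence decide whether a risk ratio or an odds ratio is reported, and at the planned effect the switch would usually occur

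*Protocol article*

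**What the plan says.** Protocol article, Primary outcomes: the outcome is whether a school implements at least four of the seven practices. Groups are compared with a generalised linear model, "a separate analysis conducted for each time point". On the link: "A log link and binomial distribution function will be used (a logistic link will be utilised if the analysis model fails convergence". On adjustment: "The stratification variables will be included in the models as covariates". Multiple imputation is the main method for missing data. The section does not say which effect measure will be reported.

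Randomisation: "Block randomisation (1:1) will be undertaken within the strata (four local health districts and two school sectors". The covariates are therefore district (four levels) and sector (two levels). The text does not say whether they enter as two main effects (four parameters) or as one eight-level factor (seven parameters).

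Sample size: "a sample of 76 schools (38 per arm) will provide 80% power" for an absolute increase of about 35 points over an assumed 40% in usual care, at alpha 0.025 because there are two time points.

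School practices: each of the seven practices is to be analysed in the same way as the primary outcome.

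**The concern.** A fallback is harmless if it is rarely used or if it estimates the same quantity. Here it estimates a different one. A log-binomial model must keep every fitted probability at or below 1. With a common outcome, few schools and several covariates, the likelihood maximum often lies on that limit and the fit fails. The reported measure then depends on a numerical property of the data set.

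What is at stake is the scale and readability of the headline result. At common outcome rates an odds ratio is much further from 1 than the risk ratio, and readers often take one for the other. The two time points are fitted separately and both carry a primary claim, so one could yield a risk ratio and the other an odds ratio. The table of seven practices could be mixed in the same way.

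**Working it through.** **Inputs from the protocol.** 76 schools, 38 per arm, 1:1; control rate 40%; program rate 40 + 35 = 75%; alpha 0.025; covariates district and sector.

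**Assumptions.** Stratum sizes are not given. The first layout used 22, 8, 16, 6, 8, 4, 8 and 4 schools. Eight further layouts used equal districts or a 45/30/15/10% split, with a Catholic share of 10, 20, 30 or 50%. The base case has no true stratum differences.

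**Step 1: the plan's own figure.** With a two-sided alpha of 0.025 (z = 2.241), 80% power (z = 0.842) and mean rate 0.575:

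n per arm = [2.241 × √(2 × 0.575 × 0.425) + 0.842 × √(0.4 × 0.6 + 0.75 × 0.25)]² / 0.35²
= [2.241 × 0.699 + 0.842 × 0.654]² / 0.1225 = 36.6, so 37.

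Power with 38 per arm = Φ[(√38 × 0.35 − 2.241 × 0.699) / 0.654] = Φ(0.903) = 0.817. The stated 80% reproduces.

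**Step 2: one result on three scales.**
- Risk difference: 0.75 − 0.40 = 35 points.
- Risk ratio: 0.75 / 0.40 = 1.875.
- Odds ratio: (0.75/0.25) / (0.40/0.60) = 3 / 0.667 = 4.50.

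**Step 3: why the log link fails.** From a program-arm rate of 75%, a combined district-and-sector ratio of 1/0.75 = 1.33 takes the fitted probability to 1. From 55% it would take 1/0.55 = 1.82. Chance variation between small strata reaches the first limit far more easily than the second.

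**Step 4: how often it fails at 40% v 75%.**

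| Covariates in the log-binomial model | Trials that fail |
|---|---|
| None | 0% |
| Sector only | about 4% |
| District only | about 27% |
| District + sector, first layout | 64% (65% in an independent repeat) |
| District + sector, eight further layouts | no interior maximum in 61-72%; Fisher scoring fails in 65-74% |
| Eight-level stratum factor, same eight layouts | Fisher scoring fails in 88-98% |

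The first-layout figure rests on 400 trials, with a simulation standard error of √(0.64 × 0.36 / 400) = 0.024. The further layouts used 800 trials each. With true stratum differences of SD 0.5 on the logit scale, the first layout gave 70%.

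**Step 5: other rates, district + sector main effects.**

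| Control / program | First layout | Equal districts, 30% Catholic |
|---|---|---|
| 40 / 65 | 36% | 38% |
| 40 / 55 | 24% | 18% |
| 40 / 40 | 9% | 6% |

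**Step 6: does the switch harm the test?** In 1,000 simulated complete-data trials at 40/75, the logistic model rejected at 0.025 in 84.1%. An unadjusted two-proportion test also rejected in 84.1%, and the two agreed in 99.8%. At 40/40 the logistic model rejected in 2.4% of 1,000 trials. A separate run gave 3.3% of 300, within one standard error of 2.5%: √(0.025 × 0.975 / 300) = 0.009.

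**The case against.** The strongest reply is that the order and the trigger are fixed in advance and the statistician is blinded to group, so nobody chooses a link by its result. Risk ratio 1, odds ratio 1 and risk difference 0 are the same null, and step 6 shows that the test survives the switch. An odds ratio that is labelled as one and printed beside the arm proportions misstates nothing. The 75% is only a detectable-effect scenario on an assumed control rate, and the stratum sizes are assumed too. All of this stands. It limits the point to the reported measure and makes the failure rate a range.

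A reader might go further in four ways that the protocol does not support:

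- **That the sample size is wrong** because it rests on "80% power to detect an absolute increase of ~ 35% between groups" while the model estimates a ratio. The null is shared and the power reproduces.
- **That the cost-effectiveness ratio is undermined.** The Cost effectiveness analysis section sets its own effect unit, "incremental cost per percent change in the proportion of schools implementing at least four of the seven PA practices", with the arithmetic mean difference in effect as denominator. That can be computed under either link.
- **That imputed data sets cannot be pooled.** This follows only if the link is chosen separately in each imputed data set. The wording can equally mean one switch for the whole analysis.
- **That the analyst gains freedom to choose.** The rule is mechanical.

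A statistical analysis plan that is not shown may name the measure. The switching rule is nevertheless stated in the protocol itself, so this is more than a detail left for later.

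**Conclusion.** The point holds as one about the reported effect measure. The protocol fixes a rule under which non-convergence moves the primary estimate from a risk ratio to an odds ratio. At its own planning rates and with main-effect strata, that would happen in roughly 60-75% of trials. The same 35-point difference would be shown as 4.50 instead of 1.88, and the two primary time points or the seven practices could end up on different scales.

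The failure rate rests on assumed stratum sizes and on program-arm success near 75%. It exceeded 50% in every 40/75 layout with both stratification variables, but the fallback is less likely than not if the program rate is well below 75%. There is no evidence of lost power or inflated type I error. Should be fixed; it does not threaten the validity of the test.

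**What to change.** Delete the link-switching rule and name one effect measure in advance for both time points and for the seven practice outcomes. Two ways would do:

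- Fit one logistic model per time point with treatment and the stratification variables. Standardise to a marginal risk ratio and risk difference, with delta-method or bootstrap intervals, and pool those across imputations.
- Fit a modified Poisson model with robust variance, which keeps the risk ratio.

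The same text should say whether strata enter as main effects or as one eight-level factor. With eight strata and small cells the logistic model can itself meet separation. No further covariate is needed for this fix.

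The cost is a few sentences and a little more analysis code. Design, sample size and data collection do not change. The change should be made before outcome data are analysed.

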**Fig. 1 Fig1:**
[figure not shown]
Consort Flow Diagram

The research will be conducted and reported in accordance with the requirements of the Consolidated Standards of Reporting Trials (CONSORT) Statement [31, 32] and the Standards for Reporting Implementation Studies (StaRI) Statement [33]. Secondary schools will be randomised to receive either the multi-component implementation support intervention, or to a control arm (usual school practices) after baseline data collection. Assessment of school PA practices will occur at baseline, 12 months (mid intervention) and 24 months. A nested study involving 15 schools per arm will be used to evaluate student level outcomes, objectively measured student PA via accelerometers (overall minutes of MVPA per day, and minutes of MVPA within school hours) and indicators of adiposity (weight, Body Mass Index (BMI)), measured at 12 and 24 months (Fig. 1). Approval will be obtained from relevant ethics committees. The trial has been prospectively registered ACTRN12617000681358.

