#### Secondary outcomes

##### School practices

Secondary outcomes will include the mean number of PA practices achieved and the proportion of schools meeting each of the practices (Table 1). Analysis will be undertaken similarly to the primary outcome, with a normal distribution function for the mean number of practices outcome.

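### School practices are measured at baseline, yet the primary and school-level secondary models name only the strata as covariates: precision is lost, validity is not

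*Protocol article*

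**What the plan says.** On timing, the Study design section states: "Assessment of school PA practices will occur at baseline, 12 months (mid intervention) and 24 months". On the instrument, the School practices section under data collection states: "Measures of the seven PA practices shown in Table 1 will be undertaken via the computer assisted telephone interviews with Head PE teachers". The section on school and Head PE teacher characteristics places that interview at baseline, 12 and 24 months. Under Randomisation, principals hear their allocation only after the baseline practice data are in.

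On analysis, the Primary outcomes section specifies a separate binomial regression at each follow-up, with a log link and a logistic link as fallback. It then gives the covariates: "The stratification variables will be included in the models as covariates". The strata are four health districts and two school sectors. For the school-level secondary outcomes: "Analysis will be undertaken similarly to the primary outcome, with a normal distribution function for the mean number of practices outcome". No section puts baseline practice into a school-level model, either as a covariate or as a repeated measure.

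**The concern.** A school that already meets several practices before the trial may well meet four of seven at follow-up whichever arm it is in. If so, the baseline score explains part of the between-school variation in the outcome, and a model without it has a wider confidence interval than the data require. Randomisation is stratified by district and sector but not by prior practice, and there are only 38 schools per arm. The arms could therefore differ noticeably at baseline by chance. A strata-only analysis would not condition on that difference, and adding the baseline score once the imbalance had been seen would be post hoc.

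The point applies only to the school-level models. Student outcomes are measured only at 12 and 24 months and have no baseline value to use.

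**Working it through.** **1. Inputs from the protocol (Sample size).** "a sample of 76 schools (38 per arm) will provide 80% power to detect an absolute increase of ~ 35% between groups"; "alpha 0.025 to allow for program effect at 12 or 24 months"; and an assumption that "40% of schools in the usual care arm achieve this target at follow-up". So p0 = 0.40, p1 = 0.75, n = 38 per arm, alpha = 0.025. Sidedness is not stated; two-sided reproduces the figure. Neither the baseline level of practice nor its correlation with follow-up is given, so both are assumed below.

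**2. Reproducing the plan's figure.** Two proportions, pooled variance under the null, no continuity correction. The pooled proportion is 0.575, z for alpha is 2.241 and z for power is 0.842.

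- n per arm = [2.241 × √(2 × 0.575 × 0.425) + 0.842 × √(0.24 + 0.1875)]² / 0.35² = (1.567 + 0.550)² / 0.1225 = 36.6, so 37 against the stated 38.
- Power at 38 per arm = Φ[(0.35 × √38 − 1.567) / 0.654] = Φ(0.903) = 81.7%.

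The stated size reproduces with no allowance for baseline adjustment.

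**3. Plausible chance imbalance at baseline.** The 95% range for the between-arm difference in the proportion meeting the target is ±1.96 × √[2p(1 − p)/38]. For baseline rates of 10%, 20%, 30% and 40% this gives ±13, ±18, ±21 and ±22 percentage points.

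**4. Number-of-practices outcome.** With a linear baseline term the residual variance is multiplied by 1 − r². For r = 0.3, 0.5 and 0.7 the factor is 0.91, 0.75 and 0.51. The standard error is multiplied by 0.954, 0.866 and 0.714, a reduction of 5%, 13% and 29%.

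**5. Primary (binary) outcome.** Simulation of 4,000 trials per setting: 38 per arm, 40% v 75%, a latent normal score at baseline and follow-up, a linear model on the binary outcome, alpha 0.025, no strata terms. The covariate is the continuous baseline score. The variance ratio is the squared ratio of the two standard deviations.

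| Latent correlation | SD of estimate, unadjusted | SD, adjusted | Variance ratio | Power, unadjusted to adjusted |
|---|---|---|---|---|
| 0 | 0.1081 | 0.1090 | 1.017 | 82.7% to 81.6% |
| 0.3 | 0.1056 | 0.1035 | 0.961 | 82.0% to 83.9% |
| 0.5 | 0.1061 | 0.0990 | 0.871 | 84.0% to 88.5% |
| 0.7 | 0.1048 | 0.0903 | 0.742 | 84.3% to 94.2% |

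True unadjusted power does not depend on the correlation; the spread in that column is simulation noise. The mean estimate was 0.35 with and without adjustment, so neither analysis is biased.

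Logistic regression with marginal standardisation (3,000 trials per setting) gave variance ratios of 1.016, 0.949, 0.880 and 0.699. Repeats with a rounded 0–7 count, some with strata terms, gave reductions of 3–6%, 8–15% and 24–29% at 0.3, 0.5 and 0.7. Hence the overall ranges 3–6%, 8–15% and 24–30%.

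Replacing the score with baseline yes/no status (30% assumed to meet the target) helps less. Power moved from 82.0% to 82.8%, 84.0% to 86.0% and 84.3% to 90.1%. This is why the count is the better covariate.

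**6. What an imbalance would do.** In simulation, a chance difference of one practice between arms at baseline shifted the unadjusted risk difference by about 7, 12 and 16 points at latent correlations of 0.3, 0.5 and 0.7.

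**7. Convergence.** With the baseline count added and no strata terms, the log-binomial model converged in about 25% of simulated trials at correlation 0.3, 5% at 0.5 and 1% at 0.7. With the strata alone it converged in about 50%.

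**The case against.** The strongest reply is that nothing here is wrong. A reader might infer that omitting baseline practice biases the estimate, or that chance imbalance goes unaccounted for. The protocol does not support that. Under randomisation the strata-only estimate is unbiased, and its standard error and type I error rate already allow for chance imbalance. A reader might also infer that the trial is underpowered without the adjustment; but 80% is the stated target and it reproduces. This part of the reply stands in full, and the point is limited to precision and conditioning.

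Second, the gain is not free and cannot be promised. The protocol has no prior data on baseline practice, so calling it the strongest predictor would be assertion. Program schools receive two years of support intended to change these practices, so a high correlation cannot be presumed, least of all in that arm at 24 months. At a latent correlation of 0.3 the gain is about two points of power. This also stands, and is why only a range is given.

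Third, the article does not say that the strata are the only covariates, and an analysis plan could add more. This has some force. But the section fixes distribution, link, fallback and covariates, and the student-level section does list prognostic covariates, so the natural reading is that the school-level list is complete. The content of the imputation model is different: the article leaves it open, and that is no finding.

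Fourth, the change costs more than one degree of freedom, because it effectively moves the first-choice link from log to logistic. That is correct and is counted below.

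**Conclusion.** The point holds as a recommended improvement, not as an error. The trial collects a pre-disclosure baseline value of its primary outcome, and the school-level models as written do not use it. The strata-only analysis remains valid. The cost of leaving it unchanged is a variance of the risk difference larger than it need be, and an estimate that does not condition on prior practice when baseline differences of 13 to 22 points lie within the 95% chance range (for baseline rates of 10% to 40%).

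The size rests on assumed correlations: small at 0.3, useful at 0.5, substantial at 0.7, and a 1–2% variance increase at zero. That baseline is unused is clear from the text; how much it matters cannot be settled from the protocol.

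**What to change.** Before any outcome data are examined by arm, prespecify the following:

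- Primary and number-of-practices models: add the baseline number of practices achieved (0–7, linear) alongside the stratification variables, at both follow-ups.
- Single-practice models: add baseline status on the same practice where cells are not too sparse, with the sparseness rule stated in advance. Some practices may be met by very few schools at baseline.
- Binary outcomes: make the protocol's logistic link the first choice and obtain the risk ratio or risk difference by marginal standardisation. This avoids reliance on a log-binomial fit that will often fail, and keeps a marginal effect in place of a conditional odds ratio.

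The cost is one extra term per model, a change of first-choice link for the primary analysis, and a negligible loss of precision if baseline practice turns out not to be prognostic. No new data are needed.
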